**Methods:**

The Stop OsteoARthritis (SOAR) study is a parallel, two-arm, assessor-blinded, superiority, hybrid effectiveness-implementation type 1 randomized controlled trial. After baseline testing, 166 participants aged 16–35 years, 9–36 months past, a first-time ACLR with ongoing symptoms will be randomly allocated to one of two treatment groups (1:1 ratio, stratified by sex). Ongoing symptoms will be defined as not meeting a Patient Acceptable Symptom State (PASS) on the averaged Knee injury and Osteoarthritis Outcome Score pain, symptoms function in sport and recreation, and quality-of-life subscales (KOOS_4_ < 79). Participants randomized to the experimental intervention will receive a digital (remote videoconferencing) 6-month program of group-based learning, individualized weekly home-based exercise therapy and physical activity program with tracking, and 1:1 physiotherapist-guided counseling. Participants randomized to the minimal intervention control group will receive an educational recording, best-practice guide for ACLR rehabilitation, one videoconferencing session, and tracking. The primary effectiveness outcome is the between-group difference in KOOS_4_ change from baseline to 6-months, with secondary endpoints at 12- and 24months. Secondary effectiveness outcomes include differences in the change of individual KOOS subscale scores, proportions of participants achieving KOOS subscale PASS scores, perceived self-management, and MRI features of knee OA. We will also assess secondary implementation (perceived barriers and facilitators of SOAR delivery), secondary efficiency (incremental cost-utility ratio), and exploratory outcomes. Missing data will be imputed and blinded intention-to-treat analyses performed.

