### Analyses {20a, b, c}

Statistical analyses will be performed by an independent statistician and then evaluated and interpreted in a blinded fashion by the author group (results will be written up as two scenarios; group A having had SOAR and group B having had SOAR) prior to breaking the randomization code [78]. To preserve study integrity and mitigate the risk of type 1 errors and premature conclusions, interim analyses are not planned.

Primary analyses will be *intent-to-treat* (by randomization) and missing data will be addressed as outlined below. We will report descriptive statistics for demographic and possible prognostic variables (socioeconomic status, sport participation, time from injury/ACLR, concomitant injury/surgery, rehabilitation, graft type, reinjury, co-interventions) for all participants, those lost to follow-up, and by study group, and consider or control for group differences when interpreting results.

SOAR superiority will be assessed with a generalized linear mixed regression model (GLMM) for the primary outcome (change in KOOS_4_ from baseline to 6 months) adjusted for continuous [153] baseline KOOS_4_ value, BMI [154, 155], time since ACLR [29], and sex. Given there is a single primary outcome, multiple comparison adjustment is not required. SOAR superiority for secondary outcomes will be assessed with mixed-effect logistic (OA lesion worsening) or linear (individual KOOS subscale scores, KOOS PASS and PIH scores) regression models adjusted for the same variables as the primary GLMM, at stated time points. To gauge the robustness of chosen PASS cut-off scores, we will perform two sensitivity analyses. First, we will consider a cut-point based on the upper bound of the PASS values 95%CI and secondly, a cut-point that would result in 10% more participants in the SOAR group achieving a PASS than the control group; a percentage agreed upon by our clinician partners as sufficient to change their management approach for this patient population considering patients SES, program costs, and the possibility of adverse events.

A strength of GLMMs is that they use all available data by including variables with missing outcome values. The relationship shape between continuous covariates and outcome change will be assessed prior to analyses. Nonlinearities will be addressed via fractional polynomial or restricted cubic spline transformations, as indicated.

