Robust statistical methods will be used to address missing data and minimize the potential for skewing results by missing data handling. GLMMs produce valid inference under the missing at random (MAR) assumption (a standard assumption and more plausible than missing completely at random). Missing values are MAR when they can be predicted from observed data (demographic/prognostic variables, outcome values). As recommended, significant demographic/prognostic and outcome variables will be included as model covariates [156]. To reduce bias and minimize statistical power loss, we will use likelihood-based direct estimation to handle missing outcome values (equivalent to imputing missing values infinite times) [157]. We will assess the robustness of estimates to MAR assumption violations with the Index of Sensitivity to Nonignorable missingness (ISNI) using the R package “isni” [158–161]). The ISNI employs selection models for non-random missing data and performs sensitivity analyses to measure any attrition bias arising from uneven study arm follow-up rates. If the missingness in demographic/prognostic variables used in the outcome models is > 5% (reducing proposed GLMM sample size), we will use a distribution-free multiple imputation method [162]. The multiple imputation method imposes no distributional assumptions on missing values, avoids implausible or out-of-range imputed values, and can handle arbitrary missing data patterns. We will examine the missingness profile and imputed values to ensure no multiple imputation bias [163, 164].

To explore the effect of gender identity (woman, man, gender-diverse) and sex (female, male, intersex), all outcomes will be described by treatment group stratified by sex or gender as appropriate, at all time points. Stratified analyses will estimate primary and secondary regression models to explore intervention effect estimates by sex (female, male) or gender (woman, man) to inform future studies. Descriptive statistics will explore differences by cis and diverse gender.

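### Missing covariates are imputed only above 5%, so a few randomised participants with an observed KOOS4 change could drop out of the primary model: small, and free to fix

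*Protocol article*

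**What the plan says.** All of the following is in the protocol article.

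- **Analyses {20a, b, c}, primary model.** The mixed model for the 6-month KOOS4 change adjusts for "baseline KOOS_4_ value, BMI [154, 155], time since ACLR [29], and sex". The primary analysis is labelled intention-to-treat, and "missing data will be addressed as outlined below".
- **Same section, missing outcomes.** "we will use likelihood-based direct estimation to handle missing outcome values".
- **Same section, missing covariates.** The condition is "If the missingness in demographic/prognostic variables used in the outcome models is > 5% (reducing proposed GLMM sample size"); when it is met, "we will use a distribution-free multiple imputation method [162". Nothing is said about covariates missing at or below 5%, or about whether the 5% is counted per variable or over the whole model.
- **Same section, further covariates.** "significant demographic/prognostic and outcome variables will be included as model covariates [156"]. These variables are not named.
- **Abstract, Methods.** "Missing data will be imputed and blinded intention-to-treat analyses performed". No threshold is mentioned.

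**The concern.** Direct likelihood uses every participant whose covariates are complete and does not need every outcome. It does not help when a covariate is blank, because the usual fit of a regression model with fixed covariates discards that row. The parenthesis in the imputation rule recognises this, since it says that missing covariates shrink the model's sample. The remedy is nevertheless withheld until the shrinkage passes 5%.

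Up to that point, a randomised participant with a known KOOS4 change can leave the primary analysis because one baseline value was not recorded. A reader of the abstract would not expect this, and an analysis by randomised group should avoid it where it can. What is at stake is a small loss of precision in the primary comparison, and in the secondary models that use the same adjustment variables.

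**Working it through.** **1. Reproduce the planned sample size** (Sample size {14}). Inputs: difference 10 points, SD 21, four covariates with combined r² = 0.3, α = 0.05, power 90%. Sidedness is not stated; two-sided reproduces the plan's figure.

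- Residual SD = 21 × √(1 − 0.3) = 17.57.
- ANCOVA power for N analysed in two equal arms: noncentral F with 1 and N − 2 − 4 degrees of freedom and noncentrality (N/4) × (10/17.57)².
- The smallest size reaching 90% is 66 per group: N = 132, noncentrality 33 × 0.324 = 10.69, power 90.05%. This matches the plan.
- 66/0.80 = 82.5, rounded up to 83 per group, or 166 in total. This also matches.

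**2. Which named covariates can be missing while the KOOS4 change is observed?**

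| Covariate | Where it is fixed | Can it be missing with the change observed? |
|---|---|---|
| Sex | Randomisation stratum (Allocation {16a, b, c}) | No |
| Time since ACLR | Eligibility criterion (Participants {10}, Table 2) | No |
| Baseline KOOS4 | Eligibility screen (Recruitment {15}) and baseline testing | No: without it there is no change score |
| BMI | Height and body mass at baseline (Outcomes {12}), before allocation | Possible, but unlikely |

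Exposure in the specified primary model is therefore essentially BMI alone. Covariates added under the further-covariates sentence could be less complete, but the article neither names them nor gives an expected rate.

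**3. Largest loss that escapes imputation, if 5% is an overall limit.**

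- 5% of 132 evaluable = 6.6, so at most 6 (4.5%), leaving 126 analysed.
- 5% of 166 randomised = 8.3, so at most 8 (4.8%). If all 8 fall among the 132 evaluable, 124 are analysed.

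| Analysed | Noncentrality | Power | Loss, points |
|---|---|---|---|
| 132 (none missing, or all imputed) | 10.69 | 90.05% | 0 |
| 126 | 31.5 × 0.324 = 10.20 | 88.7% | 1.4 |
| 124 | 31 × 0.324 = 10.04 | 88.2% | 1.9 |

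**4. Bias.** Allocation follows baseline testing, so whether a baseline value was recorded cannot depend on the assigned arm. Dropping those participants leaves a randomised comparison in a slightly smaller group.

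**The case against.** The strongest reply has three parts.

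- **Deletion is inferred.** The article never names complete-case analysis, and an analysis plan that is not shown might cover a handful of blank baseline values. This stands in part. But the article does not simply leave the matter open: it fixes a threshold, links it to loss of sample, and supplies no other covariate method, so deletion is the natural result of the rule as written.
- **The named covariates are close to complete by design.** This stands in full and is why the point is minor.
- **The prognostic variables listed in the Analyses section** (socioeconomic status, graft type, rehabilitation and others) **are for descriptive reporting and interpretation, not stated model covariates.** This also stands. They show what could be added, not what will be.

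A reader might infer two stronger things.

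- **That the intention-to-treat principle is broken.** The documents do not support this. Participants are still analysed in the arm to which they were randomised, and omission on a pre-randomisation value cannot depend on arm.
- **That the 5% applies to each covariate separately, so the losses add up over four covariates to something far larger.** The article does not say so. The parenthesis ties the limit to the model's sample, which favours an overall reading. Three of the four named covariates cannot be missing alongside an observed change score, so losses cannot accumulate over four.

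**Conclusion.** The point holds as a minor one. As written, the rule allows randomised participants with an observed KOOS4 change to drop out of the primary model when covariate missingness is at or below 5%, and this does not match the abstract's unconditional statement.

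The loss ranges from nothing, if no covariate is missing, to 6 to 8 participants and 1.4 to 1.9 power points (90.05% to 88.7% or 88.2%). The upper end assumes that the 5% is an overall limit, that missingness sits just under it, that 20% attrition has already reduced the sample to 132, and that the planning values (SD 21, r² 0.3, 10 points) hold. With BMI as the only realistic source among the named covariates, the actual loss should be nearer zero unless less complete covariates are added.

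The conclusion that this costs precision and not validity rests on the covariates being measured before randomisation. It would not automatically extend to a variable recorded during follow-up, such as co-interventions, which appear in the descriptive prognostic list. The article does not say that such a variable enters the model.

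**What to change.** Delete the 5% condition. State instead that any missing baseline covariate in the outcome models will be imputed at every level of missingness, by the multiple imputation already planned or by simple baseline imputation pooled over arms, so that every randomised participant with an observed outcome stays in the model.

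This removes the question of how the 5% is counted and brings the Analyses section into line with the abstract. It costs one sentence, needs no new method or data, and leaves the sample size unchanged.

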### Data collection procedures {11d, 18a, b}

Participants will be evaluated at baseline and 6- (primary endpoint), 12-, and 24-months (see Table 2). At all timepoints, participants will complete patient-reported outcomes using the online REDCap [77] platform and attend an in-person testing session at UBC. At the in-person session, participants will complete a computerized dynamometry assessment of knee muscle function, a bioelectrical impedance scan, and be given a triaxial accelerometer (ActiGraph wGT3X-BT®, Actigraph™, Pensacola, FL, USA) and instructed to wear it for 7 full days before returning it in a pre-paid courier envelope. The option to complete patient-reported outcomes on paper at the in-person sessions will also be offered.

At baseline, 12-, and 24-month follow-up sessions, participants will also attend a 1-hour visit to the MRI Research Centre at UBC, where dedicated technicians will collect MRI studies of the ACLR knee. Healthcare resource use (including co-interventions), monthly step count, and adverse, seriously adverse, and unexpected events will be assessed monthly over the entire study period using a 7-question short message service (SMS) screening survey and follow-up phone calls as appropriate (see below).

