#### Incremental cost-utility ratio

To assess the value for money (healthcare system perspective) of the SOAR program, we will estimate the incremental cost per quality-adjusted life years (QALY) gained by SOAR versus the control intervention at intervention cessation and end of follow-up. Costs will be estimated with a HRU questionnaire [119], as the study population often uses resources not captured in administrative data [23], and evidence of good agreement between administrative and prospectively collected HRU data [120, 121]. The HRU captures provider visits, hospital admissions, lab and diagnostic tests, and medication use. The HRU will be administered by research staff monthly via a 7-question SMS with phone call follow-up as needed over the study period.

QALYs will be estimated from health-related QOL (EQ-5D-5L) [122, 123] using area under the curve analysis. The EQ-5D-5L (European Quality of Life 5 Dimensions 5 Level) is widely used for cost-utility analyses across multiple countries and conditions [124, 125] (including OA [126, 127]), and assesses five levels across five health domains (anxiety/depression, pain/discomfort, mobility, self-care, usual activities) to produce a health state profile using Canadian conversion tariffs [128].

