The percentage of physiotherapists achieving 85% or more on the fidelity checklist and checklist items with 70% fidelity or more will be reported. Interview recordings will be transcribed and de-identified. Using a constant comparative approach [118] data will be coded and categories developed by comparing and identifying meaningful patterns across codes. High-order themes will elucidate the relationship between categories. We will look for uniqueness by gender and if found, reanalyse the data with a gender lens. Analysis trustworthiness and credibility will be fostered through data immersion, memoing, reflexive journaling and team discussions. An audit of analytic decisions will be kept [165].

Incremental cost utility ratio will be estimated as $${\mathrm{Cost}}_{\mathrm{SOAR}}-{\mathrm{Cost}}_{\mathrm{CONTROL}}/{\triangle\mathrm{QALY}}_{\mathrm{SOAR}}-{\triangle\mathrm{QALY}}_{\mathrm{CONTROL}}$$ for the intervention and post-intervention period.

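### The cost-utility denominator is a per-arm change in QALY, which area-under-the-curve QALYs leave undefined; a regression on baseline EQ-5D-5L would define it and be more precise

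*Protocol article*

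**What the plan says.** Three places in the protocol article bear on this.

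- **Incremental cost-utility ratio** (secondary outcomes). The target is the "incremental cost per quality-adjusted life years (QALY) gained by SOAR versus the control intervention at intervention cessation and end of follow-up". On measurement: "QALYs will be estimated from health-related QOL (EQ-5D-5L) [122, 123] using area under the curve analysis".
- **Analyses {20a, b, c}**, last paragraph. "Incremental cost utility ratio will be estimated as" a cost difference (SOAR minus control) over a difference in QALY terms, each carrying a change symbol, "for the intervention and post-intervention period". The text does not say what the change is measured from.
- **Analyses {20a, b, c}**, secondary-outcome models. Baseline-adjusted models are given for worsening of OA lesions (logistic) and for "linear (individual KOOS subscale scores, KOOS PASS and PIH scores) regression models adjusted for the same variables as the primary GLMM". QALYs are not on that list; their only stated rule is the subtraction above.

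On timing, Data collection procedures {11d, 18a, b} has: "Participants will be evaluated at baseline and 6- (primary endpoint), 12-, and 24-months". Patient-reported outcomes are completed at every one of these visits.

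**The concern.** A QALY total computed as an area accumulates from zero at the start of follow-up. A participant has a baseline utility but no baseline QALY, so a change in QALY within an arm is not defined until a reference is named. Subtracting control from SOAR already gives the increment. The extra change symbol is therefore either redundant (raw area) or stands for something unstated, such as area above baseline utility times duration.

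The choice matters because the denominator is likely to be small and chance differences in baseline utility are ordinary at this sample size. Two competent analysts could follow the printed rule and report different ratios from one data set. If the reading is settled after the data are seen, the result is open to selection. The cost-utility ratio is the trial's named efficiency outcome; the primary KOOS_4 comparison is not affected.

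**Working it through.** **Figures in the plan.** The documents give no utilities, utility SD, correlations or costs, so there is no cost-utility figure to reproduce. Sample size {14} gives 66 per group before attrition; 66/0.8 = 82.5, hence 83 per group and 166 in total, as stated. Utilities, SDs and correlations below are assumptions.

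**Step 1: how far the readings differ.** Let T be the duration in years and d the baseline utility difference (SOAR minus control).
- Raw reading: A = difference in mean area.
- Change reading: B = difference in mean (area − T × baseline utility) = A − T × d.

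They are equal when d = 0 and otherwise differ by T × d.

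**Step 2: an example.** Assumed mean utilities at 0, 6, 12 and 24 months are 0.80, 0.86, 0.87, 0.87 (SOAR) and 0.82, 0.84, 0.85, 0.85 (control), so d = −0.02. Trapezoid areas:
- 6 months: SOAR 0.5 × (0.80 + 0.86)/2 = 0.415; control 0.5 × (0.82 + 0.84)/2 = 0.415. A = 0.000; B = 0.000 + 0.5 × 0.02 = 0.010.
- 24 months: SOAR 0.415 + 0.4325 + 0.870 = 1.7175; control 0.415 + 0.4225 + 0.850 = 1.6875. A = 0.030; B = 0.030 + 2 × 0.02 = 0.070.

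The exact tie at 6 months follows from the values chosen. The general result is the gap of T × d.

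**Step 3: is a gap of 0.02 unusual?** The standard error of d is SD × √(2/n).

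| Assumed SD | SE of d, n = 66 | P(gap above 0.02 either way), n = 66 | same, n = 83 |
|---|---|---|---|
| 0.10 | 0.017 | 25% | 20% |
| 0.15 | 0.026 | 44% | 39% |
| 0.20 | 0.035 | 57% | 52% |

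**Step 4: what each reading does with an imbalance.** Assume equal variances and one correlation r between any two visits. The trapezoid weights are 0.25, 0.25 for 6 months and 0.25, 0.5, 0.75, 0.5 for 24 months. Given d, the expected shift in the denominator is:
- raw: d × (0.25 + 0.25r) at 6 months and d × (0.25 + 1.75r) at 24 months;
- change: the same minus d × T.

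At r = 0.4 the raw reading shifts by +0.35d and +0.95d, and the change reading by −0.15d and −1.05d. With d = 0.02 that is +0.007 against −0.003 QALY at 6 months, and +0.019 against −0.021 at 24 months. The first under-corrects and the second over-corrects.

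**Step 5: precision.** Each standard error is √(2/n × V), with n = 66 and SD s = 0.15. At 6 months:
- raw V = 0.125 s²(1 + r);
- change V = 0.125 s²(1 − r);
- adjusted for baseline V = 0.0625 s²(1 − r²).

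At 24 months:
- raw V = s²[1.125(1 − r) + 4r];
- change V = 4.125 s²(1 − r);
- adjusted V = s²[1.0625(1 − r) + 3.0625 r(1 − r)].

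| Horizon, r | Raw | Change | Adjusted |
|---|---|---|---|
| 6 months, 0.4 | 0.011 | 0.007 | 0.006 |
| 6 months, 0.6 | 0.012 | 0.006 | 0.005 |
| 24 months, 0.4 | 0.039 | 0.041 | 0.031 |
| 24 months, 0.6 | 0.044 | 0.034 | 0.028 |

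Adjustment lowers the standard error against raw by 45–55% at 6 months and 22–36% at 24 months, and against change by 11–16% and 16–26%. These percentages depend on r only; s cancels.

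**Step 6: regression removes the ambiguity.** With baseline utility in the model, subtracting T × baseline utility from the outcome alters only the baseline coefficient. The arm coefficient is the same under either reading.

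**Step 7: the time windows.** The outcome section gives two horizons, "at intervention cessation and end of follow-up". The Analyses wording could mean these, or 0–6 and 6–24 months separately. If the latter, a further reading (area above the utility at the start of the period) opens. Take assumed utilities of 0.80, 0.86, 0.86, 0.86 against 0.80, 0.82, 0.82, 0.82, with equal baselines. The 6–24 month increment is 0.04 × 1.5 = 0.06 QALY as area, and 0 as change from month 6.

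**The case against.** The strongest reply is that this is loose notation. The outcome section defines QALYs by area and names the target as cost per QALY gained, so the change symbol can be taken to mean QALYs accrued over the horizon. That is a coherent reading. But the same phrase fits QALYs above the baseline level, and nothing in the article chooses between them.

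Second, regression adjustment is a detail an article may leave to a fuller protocol or analysis plan, and Study design {8} commits to health-economic reporting standards. A reader might infer that the trial has ruled out adjustment; the documents do not say so, and silence alone would not be a finding. What stands is that the article prints an estimator, a plain subtraction of an undefined quantity, which any later plan would have to reinterpret.

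Third, a reader might infer that the ratio will be biased. It will not be on this account: over randomisations, raw area, change and adjusted regression share the same expected incremental QALY. The issue is definition, sensitivity to chance imbalance and precision.

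Fourth, a reader might infer from the Analyses wording a ratio for months 6–24 that leaves out programme costs. The article does not commit to one; the wording can equally mean the two horizons, and resource use is recorded monthly throughout. This is an ambiguity, not a proven error.

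Last, the printed formula has no brackets. The outcome section makes a ratio of differences clear and typesetting may explain it, so nothing rests on that.

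**Conclusion.** The point holds in a limited form. The printed denominator is undefined, because the QALYs it takes a change in are areas with no baseline value. The two main readings coincide when baseline utilities are equal and otherwise differ by T × d: half the baseline gap at 6 months and twice it at 24 months. A gap above 0.02 has a probability of about 20–57% for an assumed SD of 0.10–0.20 and 66–83 per arm. Both readings are less precise than baseline-adjusted regression: about 0.011 and 0.007 against 0.006 QALY at 6 months, assuming SD 0.15, 66 per arm and correlation 0.4. The sizes rest on these assumptions and on equal correlation between visits; the algebra does not. No cost-per-QALY figure is relied on, because the documents supply neither costs nor utilities. The matter concerns a secondary outcome and is worth correcting because the better method costs nothing.

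**What to change.** In Analyses {20a, b, c}:

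1. Drop the per-arm change. Define the incremental QALY as the arm coefficient from a regression of each participant's area-under-the-curve QALYs on arm, baseline EQ-5D-5L utility and sex (the stratification factor in Allocation {16a, b, c}).
2. Replace the wording on periods with the two horizons of the outcome section: costs and QALYs are both cumulated from randomisation to 6 months, and from randomisation to 24 months.

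The cost is a change to one formula and one sentence, and one regression on data already collected. No further participants, visits or measurements are needed. It should be settled before unblinded cost or utility data are seen.
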